## Abstract

**Background:**

Chronic headache (headache ≥ 15 days/month for at least 3 months) affects 2–5% of the general population. Medication overuse contributes to the problem. Medication-overuse headache (MOH) can be identified by using the Severity of Dependence Scale (SDS). A “brief intervention” scheme (BI) has previously been used for detoxification from drug and alcohol overuse in other settings. Short, unstructured, individualised simple information may also be enough to detoxify a large portion of those with MOH. We have adapted the structured (BI) scheme to be used for MOH in primary care.

**Methods/Design:**

A double-blinded cluster randomised parallel controlled trial (RCT) of BI vs. business as usual. Intervention will be performed in primary care by GPs trained in BI. Patients with MOH will be identified through a simple screening questionnaire sent to patients on the GPs lists. The BI method involves an approach for identifying patients with high likelihood of MOH using simple questions about headache frequency and the SDS score. Feedback is given to the individual patient on his/her score and consequences this might have regarding the individual risk of medication overuse contributing to their headache. Finally, advice is given regarding measures to be taken, how the patient should proceed and the possible gains for the patient. The participating patients complete a headache diary and receive a clinical interview and neurological examination by a GP experienced in headache diagnostics three months after the intervention. Primary outcomes are number of headache days and number of medication days per month at 3 months. Secondary outcomes include proportions with 25 and 50% improvement at 3 months and maintenance of improvement and quality of life after 12 months.

**Discussion:**

There is a need for evidence-based and cost-effective strategies for treatment of MOH but so far no consensus has been reached regarding an optimal medication withdrawal method. To our knowledge this is the first RCT of structured non-pharmacological MOH treatment in primary care. Results may hold the potential of offering an instrument for treating MOH patients in the general population by GPs.

**Trial registration:**

ClinicalTrials.gov identifier: NCT01314768

## Background

Headache is a common health problem and the personal burden, social impact and economic cost for both the sufferers and society are substantial 
[1,2]. Most common headaches are episodic tension-type headache (TTH) and migraine 
[3]. However, 2–5% of the world’s population have chronic headache 
[4-13] defined as 15 or more headache days per month for at least 3 months and/or 180 or more headache days per year.

Headache is mostly self-managed 
[14,15] and headache prescription medications account only partly for the total medication use for headache since most patients buy over-the-counter (OTC) drugs 
[5,6,16-19]. Headache accounts for 4% of the general practitioners (GPs) consultations 
[19], and is probably the most common reason for referral to neurologists 
[19,20]. Approximately 20–30% of all new referrals to out-patients neurological departments are due to headache 
[21,22].

Analgesic use, misuse and overuse represent major health problems associated with numerous adverse health consequences. A population-based study from Norway which included about 50,000 subjects found that 10% reported taking analgesics currently on a daily basis and up to 5% reported taking analgesics on a daily basis for at least six months 
[23]. Results from another Norwegian study showed that 28% of men and 13% of women had used analgesics over the preceding 28-day period, mostly to treat headaches 
[24]. Frequent intake of analgesics may, however, worsen headache and lead to chronification and Medication Overuse Headache (MOH) 
[25-27]. MOH is a condition with chronic headache in combination with overuse of acute headache medication(s) 
[25-27]. The prevalence of MOH in the general population is 1–2% 
[5,6,10,25-28]. The condition was first described for egotamines in 1951 
[29] and it is now substantiated that all drugs used for the acute treatment of headache can cause MOH in patients with a pre-existant headache disorder 
[25-27]. The proportion of MOH is lower in the general population than one sees in clinical settings, and the distribution of the overused medication differs with simple analgesics being most frequently overused in the general population 
[7,9,17,28,30-35].

The aims of MOH management are 
[36,37]

i. withdrawal of the overused drug(s)

ii. to provide the patient with pharmacological and non-pharmacological support

iii. to prevent relapse

Detoxification from the overused medication often leads to headache improvement 
[25,26,31,38], but is often complicated by temporary withdrawal symptoms such as worsening of headache, nausea, vomiting, hypotension, tachycardia, sleep disturbances, restlessness, anxiety and nervousness which typically occur 2–10 days after detoxification 
[26,27,40,41]. There is no established optimal withdrawal method for MOH though many different strategies have been suggested 
[25,36,37,39]. These include use of antiemetics and/or neuroleptics to reduce abstinence-like symptoms, intravenous administration of ergotamines and substitution of the offending painkiller with another. Steroid treatment has also been used to alleviate withdrawal reactions though this strategy is controversal 
[36,37,41-43].

Regarding prophylactic headache medication, there is also an ongoing discussion whether this should be initiated immediately at withdrawal or after completed withdrawal therapy 
[36,44].

Follow-up studies of various duration have reported relapse rates between 20–60% and findings from these studies suggest that patients have the highest risk of relapse within the first year after withdrawal 
[37,45-49].

MOH is a heterogenous disorder which has been suggested to include both subgroups with simple medication overuse as well as more complex detoxification-resistant cases 
[36,50-52]. Some of these cases may be more “dependency-like” and it has indeed been suggested that MOH shares some common neurobiological pathways with drug dependence and that MOH therefore may represents a kind of addictive behaviour 
[53]. Whether this applies to all MOH cases or specific subgroups defined by this particular “dependency-like” behaviour (eg. “complex” MOH) remains to be demonstrated. Two studies have demonstrated that most MOH patients fulfill criteria for dependency according to the Diagnostic and Statistical Manual of Mental Disorders, fourth edition (DSM-IV) 
[54-56]. Another study found that the dependency score based on the Leeds Dependency Questionnaire was similarly increased in MOH patients and illegal drug addicts 
[57].

Over the past decades several dependency assessment scales have been developed. The Severity of Dependence Scale (SDS) is a simple, validated scale which scores psychological dependence on a number of different substances 
[58-63]. Previous studies from our group have revealed that the SDS has both high sensitivity, specificity, positive and negative predictive values for detecting persons with MOH among chronic headache patients. 
[30,35,64]. In addition, the SDS score has been shown to predict likelihood of successful detoxification in a general population 
[65].

Screening and Brief Intervention (BI) is a well-known approach to identify and treat unhealthy alcohol use 
[66]. The SDS and similar scales such as the Alcohol Use Disorders Identification test, have previously been used to identify individuals at risk for addiction-related problems 
[58-63,67-69]. BI involves the use of such an identification tool followed by feedback to the identified individual as being “at risk”. The final step, in this very short and simple intervention is to give information suggesting to cut down the use of the particular substance to predecided “acceptable” levels 
[66]. BI includes clear directive advice, but focus is also on increasing patients insight and awareness regarding overuse as described in more detail elsewhere 
[66,70]. The BI method has shown promising results with both short- and longlasting reduction of alcohol intake and levels of related biochemical markers such as liver transferase levels 
[66,71-73]. Similar methods have also been successfully applied for various other addictive drugs 
[70,74,75].

We have previously reported data from an open, un-controlled study of medication overuse headache in the general population, which suggested that three out of four MOH subjects had managed to reduce their medication intake after short information 
[76]. Similar simple advice also works in clinic settings 
[77,78]. One population- and one clinic-based study suggest that MOH can be successfully managed in a primary care setting after an initial collaboration with headache specialists 
[45,79].

The common headache disorders require no high-tech investigations and may therefore be diagnosed and managed by all skilled physicians. Most headaches are therefore probably best managed in primary care. Focus on MOH in primary care is therefore important both in order to prevent MOH from developing and for early diagnosis and treatment.

We have designed a BI for treatment of MOH in primary care and planned a double-blinded cluster randomized parallel controlled trial (RCT) to evaluate effects of the intervention.

### Objectives

The primary objective is to evaluate the effects of a brief intervention (BI) versus business as usual (BAU) in the management of MOH in primary care.

## Methods/Design

Our hypothesis is that BI is more effective than BAU. The hypothesis will be tested using a double-blinded cluster randomised parallel controlled clinical trial in primary care comparing BI and BAU three months after study inclusion and with additional open one year follow-up (Figure 
1).

**Figure 1 F1:**
[figure not shown]
**Flow-chart of study*****.*** Figure illustrates main time line with the different phases with those mainly responsible for each phase (lower part). Upper part shows time-points for Patients data collection (2 week headache diaries (2w.diary) and interviews) as well as timing of various moments for the Investigator group and GPs with Brief Intervention training courses (BIC) for GPs and intervention (Brief intervention - BI and Business as usual – BAU respectively). Main outcome time-point at 3 months depicted with double arrow and bold writing. BI, Brief intervention; BIC, Brief Intervention course early or late; BAU, Business as usual; GP, General practitioner; Rand, randomisation.

### Setting

The Norwegian GP list-patient system was established in 2001. The GPs are reimbursed through a fixed annual fee and fees for the specific services from the National Health Insurance and the patients. GPs act as gate keepers for referrals to secondary care specialists and hospitals except in emergencies. GP specialists must renew their specialty every fifth year. As a part of this process, clinical training courses and participation in peer continuous medical education (CME) group meetings are compulsory. GPs in the same practice often attend the same peer CME group, each group typically comprised of four to ten GPs from different practices. The study will be undertaken among GPs attending CME groups in south-eastern Norway.

### Recruitment, randomization and blinding

#### GPs

Recruitment of the GPs will be done by inviting a number of GPs’ peer CME groups to a Brief Intervention Course (BIC). Randomisation of GPs (and thereby their patients) to either BI or BAU will be performed by an external statistician. Each GP and his/her patients defines one cluster. For practical reasons and to avoid carry-over effects, the CME groups will be the randomisation unit.

GPs in half of the CME groups will receive the BIC and apply BI on their own patients, while the others will run their clinical practice as usual (BAU).

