#### Statistics

All analyses will be focused at the patient level (inference unit will be patient). We will perform a series of frequency analyses tabulating outcome variables against various explanatory variables and/or confounders. Suitable descriptive statistics will be used. Since individual observations within the same cluster (ie. patients of one GP) may be correlated, the intra-cluster (intra-class) correlation coefficient (ICC) measuring such a “clustering effect” and estimating the relative variability within and between clusters will be calculated for both intervention- and control groups. Analysis of differences between BI- and BAU groups based on mixed linear models (MLM) will be performed to account for the hierarchical nature of data, where the main point is to allow variation to be modelled at each level of the data, for example, the GP and the patient level. 95% confidence intervals will be used.

Analysis based on prespecified hypotheses regarding the two primary and the secondary outcomes will be performed as hypothesis testing on the entire dataset and Bonferroni corrections will be used for multiple comparisons. For evaluation of possible outcome predictors where no prior data from this population exist, split file analysis 
[103] will be used. The splitting of the data set will be performed prior to any analyses of primary and/or secondary outcomes.

The intention-to-treat principle will be followed by including all patients with at least one follow-up response. Missing values will be handled using multiple imputation techniques.

SPSS 16.0 and SAS will be used for statistical analyses.

Registration of electronic data from the semi-structured interviews will be done by using Snap Survey (Snap Survey, London, UK).

The participating patients will receive a weekly reminder regarding the headache diary via mobile phone (SMS) during each two weeks diary period at three, six and twelve months, respectively.

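### CME groups are randomised, but the cluster definition, ICC and sample size are set at GP level; if GPs within a CME group are correlated, the GP-level precision and stated power are too favourable

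*Protocol article*

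**What the plan says.** The GPs subsection of Recruitment, randomization and blinding sets out two units side by side. On analysis units it says "Each GP and his/her patients defines one cluster". On allocation it says "For practical reasons and to avoid carry-over effects, the CME groups will be the randomisation unit", and then "GPs in half of the CME groups will receive the BIC and apply BI on their own patients".

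The Setting section describes a CME group: "each group typically comprised of four to ten GPs from different practices". It adds that "GPs in the same practice often attend the same peer CME group".

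The Power calculations section counts clusters as GPs, takes a worst-case ICC of 0.5 and settles on 20 physicians and 160 patients. The Statistics section places the ICC at the same level ("Since individual observations within the same cluster (ie. patients of one GP) may be correlated") and describes mixed linear models that "allow variation to be modelled at each level of the data, for example, the GP and the patient level". Neither section gives the CME group a variance term or a count, and the number of CME groups appears nowhere in the article.

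**The concern.** In a cluster trial, the precision of the treatment contrast is governed by the number of randomised units and the variation between them. Here those units are CME groups. A model with only a GP effect treats GPs in the same group as independently allocated. If they share anything that affects outcome, such as practice, catchment area or prescribing habits, the standard error of the BI-versus-BAU difference is too small and its degrees of freedom too many.

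Both primary comparisons depend on this. Under Ethics and data security, a significant benefit at three months may also lead to BI being offered in the control arm. Separately, the stated power rests on 20 units, while the number actually randomised is smaller and unknown.

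**Working it through.** **Inputs from the protocol.** Power 80%; significance level 5% (two-sided assumed, as sidedness is not stated); 18 patients per arm unadjusted for medication days; m = 8 patients per GP; within-GP ICC 0.5; 20 GPs and 160 patients; four to ten GPs per CME group.

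**Inputs assumed.** The CME-level variance share and the number of CME groups are not in the document. I use 4 groups of 5 GPs as the main illustration and 10 groups of 2 for contrast.

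**Step 1: reproduce the planned size.** Design effect at GP level = 1 + (m − 1) × ICC = 1 + 7 × 0.5 = 4.5. Then 18 × 4.5 = 81 per arm, or 162 in total, against the stated 160. The 20 GPs provide an effective 80/4.5 = 17.8 patients per arm. The GP-level correlation therefore uses up the whole sample, and nothing is left for a CME term.

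**Step 2: number of randomised units.** If whole groups take part, 20/10 = 2 to 20/4 = 5 CME groups in total.

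**Step 3: type I error of a GP-level test.** I simulated trials with no true effect, 20 GPs × 8 patients, and a t test on GP means at nominal 5%. With balanced data this corresponds to a GP random-intercept model.

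| CME share | GP-only share | 4 groups × 5 GPs | 10 groups × 2 GPs |
|---|---|---|---|
| 0 | 0.50 | 5% | 5% |
| 0.01 | 0.49 | about 6% | about 5% |
| 0.02 | 0.48 | about 7% | about 5% |
| 0.05 | 0.45 | about 9% | about 6% |
| 0.10 | 0.40 | about 14% | about 7% |
| 0.01 | 0.04 | about 8% | about 6% |
| 0.05 | 0.05 | 17–18% | about 8% |

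A t test on CME-group means stays at about 5% in every row.

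Bonferroni correction does not remove the problem. At CME share 0.05 and total within-GP ICC 0.5 with 4 groups, a nominal 2.5% GP-level test has a true error of about 5.5%.

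**Step 4: effective sample size with a CME term.** For k GPs per group, design effect = 1 + (m − 1) × ICC_GP + m(k − 1) × ICC_CME, where ICC_GP is the total within-GP correlation. With m = 8, k = 5 and ICC_GP = 0.5:

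- ICC_CME 0.05: 1 + 3.5 + 32 × 0.05 = 6.1; effective n per arm 80/6.1 = 13.1
- ICC_CME 0.10: 1 + 3.5 + 32 × 0.10 = 7.7; effective n per arm 80/7.7 = 10.4

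The requirement is 18 per arm.

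**Step 5: power of a valid test with 2 versus 2 groups.** The standardised effect that 18 per arm detects with 80% power is (1.96 + 0.842) × √(2/18) = 0.93 by the normal approximation, or 0.96 by the t distribution. The CME-level test has 2 degrees of freedom and critical value 4.30. Its noncentrality is the effect divided by √(2/effective n); at effective n 17.8 and effect 0.96 this is 2.87. Using 0.96 (0.93 in brackets):

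- ICC_CME 0: about 36% (35%)
- ICC_CME 0.05: about 29% (28%)
- ICC_CME 0.10: about 25% (24%)

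Most of the loss comes from the degrees of freedom, since power is already 36% with no CME variance. A lower GP correlation does not restore 80%: with within-GP ICC 0.1 and ICC_CME 0.01, the same test has about 59% power (effect 0.93).

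**The case against.** The strongest reply concerns the model. The Statistics section speaks of "variation to be modelled at each level of the data, for example, the GP and the patient level", and the words introducing the two levels make them illustrations. A CME level is not excluded, and the full model may be specified in an analysis plan that is not shown. This stands. A reader might infer that the protocol has fixed a two-level model and that type I error will exceed 5%, but the text supports neither. Inflation needs both a model without the CME level and CME variance above zero. At zero variance the GP-level test keeps its 5%, and at a share of 0.01 with within-GP ICC 0.5 it is only about 6%.

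A reader might also take the stated wish to avoid carry-over as an admission that GPs within a group are correlated. The Patients subsection uses the term for information passing from BI to BAU, which is contamination between arms. It says nothing about correlation among GPs in the same arm. The better evidence is the remark in Setting about practice colleagues sharing a group.

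The count of 2–5 units is likewise conditional. GPs volunteer, so groups may take part incompletely and more groups may be recruited.

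Finally, ICC 0.5 is called a worst case, and the 20 physicians are also meant to absorb unknown carry-over. The ICC is a planning value for patients within a GP. It does not enter the fitted standard error and adds no randomised units.

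None of these replies touches the cluster definition, the ICC level or the sample-size calculation, all of which are stated at GP level.

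**Conclusion.** The mismatch is in the text and should be corrected: one unit is randomised, while the cluster, the ICC and the sample size are set on a smaller one. The stated power therefore rests on the wrong number of units, whatever model is finally fitted.

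The risk to type I error is conditional. With 4 groups of 5 GPs it runs from none at zero CME variance, through about 6–9% at CME shares of 0.01–0.05 with total within-GP ICC 0.5, to about 18% if the CME and GP shares are both 0.05. That upper figure assumes CME variance as large as GP variance, for which the document offers no support. With 10 groups of 2 GPs the range is about 5–8%.

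The power shortfall (about 25–36% against 80%) applies to a 2-versus-2 split, which is an assumption. It would be smaller with more groups.

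**What to change.** - In the mixed model, name the CME group as a random effect above the GP, with Kenward–Roger or Satterthwaite degrees of freedom. Alternatively, analyse CME-group means.
- Report the CME-level ICC alongside the GP-level one.
- State the number of CME groups, in total and per arm.
- Restate power on that number, over a range of CME-level ICCs.

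The wording changes are small. The cost is wider intervals and, if groups are few, clearly lower stated power. Spreading the 20 GPs over more CME groups would help, but it means enrolling only part of each group. That is a design trade-off for the sponsor to weigh and is not needed to correct the analysis.

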#### Patients

A short validated screening questionnaire for headache 
[80,81] including questions about headache frequency, intensity (as recorded on a visual analogue scale (VAS) 
[82]), presence of migraine and medication use will be mailed to all 18–50 year old patients on participating GPs’ patient lists. Names and addresses will be extracted from GP lists using a specially designed software (Mediata Ltd, Tønsberg, Norway). One written reminder will be sent to non-responding patients.

All patients with 15 or more days with self-reported headache per month and headache medication utilization on 10 days or more per month will be invited to participate.

Patients unable to participate in an interview in Norwegian will be excluded.

Baseline patient information (screening questionnaire and headache diary) will be collected by the Akershus University hospital research administration unit before any study-related contact between patient and their GP.

To avoid unblinding and carry-over of information from the BI to BAU, both GPs and patients will initially only receive basic information that this study aims to evaluate headache and headache care in primary care.

After the intervention part, all follow-ups will be conducted by the first author ([name]), who will be blinded in relation to which treatment the participant has received. All participating patients will receive a semi-structured interview and clinical and neurological examination.

#### Population controls

1. Control group; random sample without chronic headache (headache if present must be <15 days per month) based on the screening questionnaire. This group will be used to control for burden of headache in terms of quality of life and costs. It will also be used for drop-out analyses.

2. Chronic headache control group; random sample with headache ≥15 days per month but without medication overuse based on the screening questionnaire. This group will be used as a control for the natural course of chronic headache as well as for drop-out analyses.

